## Discussion

Based on our literature review, this is the first study that will combine a dietary supplement based on SPMs with telerehabilitation to reduce the symptoms of patients with PCC. The effectiveness of a nutritional over only a physiotherapeutic intervention would open a field of intervention for these patients who still do not have an effective treatment.

Statistical improvements in quality of life are expected in the Nutritional supplement group to be linked to the improvement of the inflammatory profile although changes are expected in both groups. Specialized nutrition with SPMs might have favorable effects on PCC symptoms due to the potential mechanisms of action for omega-3 acids and their metabolites [25,58]. These actions will result in clinical improvement and therefore in the quality of life perceived by patients. In this regard, Pavlidou’s review confirms that this type of supplementation is beneficial before and during COVID-19 disease and encourages studies like this one to show its effect in patients with PCC [59]. In addition to the nutritional supplement, pulmonary rehabilitation and controlled aerobic and strength training seem to be the most effective interventions used to improve the symptoms of PCC [60]. Furthermore, telerehabilitation has already been shown to be effective in improving quality of life in a similar way to face-to-face treatments, as reported by Dias et al. 2021 in a systematic review [61].

It is expected to have a reduction of long-lasting inflammation in NG for the anti-inflammatory effect of omega-3 [62] by blocking the inflammasome activation and pro-inflammatory cytokine production, thereby restoring tissue homeostasis; improving innate immunity; and reducing oxidative stress by controlling the activity of related enzymes and the generation of free radicals (ROS) [63]. Although the effectiveness of SPMs in reducing inflammation in these patients is not yet proven, in vitro studies show that both Resolvin D1 and Resolvin D2 are potent in reducing the production of pro-inflammatory cytokines, showing the potential role of lipid mediators in the treatment of PCC [64]. The favorable effects of physical exercise on the reduction of inflammation, as well as the modulation of cytokines, have been widely reported in different fields [65,66]. Therefore, improvements can be expected in both groups, although NG will show greater changes, due to the sum of two interventions with anti-inflammatory potential.

This expected improvement in the inflammatory balance in NG will be linked to major improvements in fatigue and dyspnea levels, functional status and psychosocial variables. The presence of sustained low-grade inflammation in these patients is a limitation that physical rehabilitation faces today in improving its effectiveness, especially as this inflammatory cascade leads to an increase in perceived fatigue [67]. It is already known that the fatigue characteristic of PCC is similar to chronic fatigue syndrome, which is also characterized by emotional and mental disturbances. Fatigue severity has been significantly correlated with increased monocytes, up-regulation of CCL2, CCL7 and SERPINB2 gene levels in monocytes, increased serum galectin-9 and increased CD8+ T-lymphocyte counts. Likewise [68], other nutritional supplements such as L-arginine plus vitamin C or anhydrous enol-oxaloacetate have been shown to be effective in controlling/relieving PCC and thus, a reduction in fatigue [69–71]. Other studies have established the benefits of vitamin and mineral supplements, particularly vitamin C, vitamin D, zinc and selenium, or multivitamins with flavonoids such as quercetin and bromelain [67].

In terms of respiratory strength and functional status, positive changes can be expected in both groups, even if they will be particularly relevant for NG. There are no studies on the benefits of omega-3 supplementation for PCC, but a recent meta-analysis has shown that there are benefits for muscle mass and performance (walking speed) in older people [72]. As for other supplements, a small group of COVID-19 survivors in a pre-post study showed an improvement in muscle strength and physical performance with a dietary supplement containing 19 nutrients, including amino acids such as arginine and carnitine, minerals, B-group vitamins, and plant extracts. Although the study showed positive results, there was no control group, and no exercise program like ours was proposed [73]. In addition, according to the latest systematic review, pulmonary rehabilitation has proved to be effective in the different stages of COVID-19, which leads us to assume that MIP-MEP, dyspnea, and functional status could improve in both groups [74].

Related to the inflammatory mechanism and mental health, kynurenine, a metabolite increased in COVID-19 patients, is associated with depression states and contributes to oxidative damage in the brain (neuroinflammation). In contrast, kynurenic acid cannot cross the blood-brain barrier, protecting the brain from depression [75,76] Reducing inflammation with EPA/DHA fatty acids combined with exercise can increase the conversion of kynurenine into kynurenic acid in the skeletal muscle and improve emotional symptoms. Although a recent review has concluded that omega-3 fatty acids deficiency is associated with an increased risk of mental disorders [77], there are currently contradictory results on the effectiveness of omega-3 on depressive symptoms, with variable factors such as dosage and patients’ baseline diet being the cause of these contradictions [78]. However, we expect that the mental health of patients with PCC of NG will improve significantly thanks to nutritional supplementation and telerehabilitation, as exercise has been proposed as a good strategy for neurological recovery from COVID-19 sequelae.

For all the above reasons, the combination of SPMs supplementation and telerehabilitation would be a promising strategy to improve the physical and mental health of patients with PCC.

### Strengths and limitations

The limitations of this study may be the problems of patient recruitment, as the sampling is of convenience, there may be a bias of participation of those patients who are more symptomatic and better adherent due to their interest in participating, and by design, we cannot know the effect of tele-rehabilitation versus only giving recommendations or the effect of nutritional supplement enriched in SPMs in isolation. Furthermore, because of the multiple contrasts due to the large variety of variables, a significance of 95% could increase the type I error.

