**Methods:**

ARACOV-2 study is a double-blind, parallel-group, randomized control trial with two parallel interventions: Nutritional supplement and telerehabilitation vs placebo supplement and telerehabilitation. The primary endpoint will be quality of life (EQ-5L-5D). The intervention will last 12 weeks with a daily intake of omega-3 or placebo and a daily supervised rehabilitation programme using telerehabilitation.

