#### Secondary outcomes.

**Inflammatory and pro-resolving profile:** Behind the symptoms of PCC lies an unresolved inflammatory cascade. Since SPMs are considered to be pro-resolving inflammation, it was considered to analyze the change in this inflammatory profile [25–27]. The analyzed parameters will be: cytokines: IL-1, IL-2, IL-4, IL-6, IL-8, IL-10, IL-17A TNF-α, and interferon-gamma (IFN-γ); free fatty acids: EPA, DHA, arachidonic acid (ARA), (DPA) and monohydroxylated lipid mediators (LMs): 17-HDHA, 18-HEPE, 14-HDHA; resolvins (Rv): EPA-derived RvE1, RvE2 and DHA-derived resolvins (RvD): RvD1, RvD2, RvD3, RvD4, and RvD5; maresins (MaR): MaR1, and MaR2; protectins: PD1 and PDX; lipoxins (LX): LXA4, and LXB4; prostaglandins: PGE2, PGD2 and PGF2α; thromboxane TXB2; and leukotriene LTB4.

Blood samples for cytokine analysis, will be centrifuged for 15 minutes at 1000 x g. Then, the serum will be removed, aliquoted and stored at −80°C until cytokine measurement. IL-6 will be measured by enzyme-linked immunosorbent assay using the Quantikine® HS Human Immunoassay Kit (HS600C, R&D systems) according to the manufacturer’s recommendations by using a Biotek Synergy HT Microplate Reader. The rest of the cytokines will be determined by using the Human XL Cytokine Luminex® Kit Performance Assay (FCSTM18B, R&D Systems) according to the manufacturer’s recommendations and analyzed with a LABScan 100 Multiplexing Analyzer System (Luminex Corporation).

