#### Fatigue.

Fatigue will be measured with the FSS [34], a self-reported scale that allows assessing the severity of fatigue as a sense of physical tiredness, muscle weakness and lack of energy. It has been validated in post-COVID patients [35]. It is composed of 9 items with scores ranging from 1= strongly disagree to 7= strongly agree. The higher the number, the greater the severity of fatigue. The most common cut-off point is a mean score of 4 points, considering equal or more than 4 as severe fatigue [36].

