#### Statistical analysis.

Statistical analysis will be performed with IBM-SPSS Statistics software version 25 or later. Quantitative variables will be described as mean and standard deviation (SD) if the variable follows a normal distribution or as median and interquartile range for non-normal data. For categorical data absolute and relative frequencies will be computed. The Kolmogorov-Smirnov test will be used to determine the normality of the data. Intra-group variables will be measured with the T-Student test for related samples or the paired samples Wilcoxon test for non-parametric alternative. For inter-group comparations non-parametric analysis will be performed when a non-normal distribution is assumed, using the U Mann Whiney test for comparisons between groups and T-Student test for normal data. Dichotomous variables will be analyzed using the chi-square test. A significant level of 95% will be assumed (p <0.05). If there are more than 15% dropouts, an intention-to treat (ITT) analysis will be performed. Effect size will be calculated using Cohen’s d to determine clinical significance: negligible, small, medium and large differences will be reflected in effect sizes of < 0.2, 0.2–0.5, 0.6–0.8 and > 0.8, respectively.

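### One unadjusted p<0.05 covers 34 analytes and 9 clinical secondary measures; the article concedes the inflated type I error but gives no rule to deal with it

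*Protocol article*

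**What the plan says.** The Statistical analysis section gives one level for all testing: "A significant level of 95% will be assumed (p <0.05". It names between-arm tests and within-arm paired tests. It does not rank the secondary outcomes, call any of them exploratory, or adjust for their number.

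Strengths and limitations returns to the subject and accepts that "because of the multiple contrasts due to the large variety of variables, a significance of 95% could increase the type I error". No correction, hierarchy or reporting rule follows.

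The abstract names one primary instrument: "The primary endpoint will be quality of life (EQ-5L-5D". Everything counted below is listed under Secondary outcomes or the headings that follow it, from Fatigue to Psychosocial factors.

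**The concern.** Convenience sampling, named in the same paragraph, cannot be undone at the analysis stage. Multiplicity can: it follows from the decision rule, and the decision rule is a matter of wording. The article states the rule, states its consequence, and stops there. This is therefore more than a detail left to a statistical analysis plan that is not shown.

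What is at stake is how the secondary results are read. With a panel of 34 analytes and no rule for which of them count, a handful of nominally significant results can be expected by chance. The reader of the final report would have no pre-stated basis for telling these from real effects. The Discussion expects improvement in inflammatory balance to go together with improvement in fatigue, dyspnea, function and psychosocial measures, so the analyte results will matter to the interpretation.

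**Working it through.** **The plan's own figure.** The article gives no family-wise error figure to reproduce. Its sample size can be checked, to see whether the primary comparison stands on its own. Inputs from Sample size calculation: 30% against 50% improved, two-sided alpha 0.05, power 80%, 15% loss.

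- n per arm = [1.960 × √(2 × 0.40 × 0.60) + 0.842 × √(0.30 × 0.70 + 0.50 × 0.50)]² / 0.20² = 93
- 93 / (1 − 0.15) = 109.4, rounded up to 110, as stated.

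The primary calculation reproduces at alpha 0.05 and does not depend on the secondary family.

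**Count of secondary outcomes.**

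- "cytokines: IL-1, IL-2, IL-4, IL-6, IL-8, IL-10, IL-17A TNF-α, and interferon-gamma (IFN-γ": 9
- "free fatty acids: EPA, DHA, arachidonic acid (ARA), (DPA) and monohydroxylated lipid mediators (LMs): 17-HDHA, 18-HEPE, 14-HDHA": 4 + 3 = 7
- "EPA-derived RvE1, RvE2 and DHA-derived resolvins (RvD): RvD1, RvD2, RvD3, RvD4, and RvD5": 2 + 5 = 7
- Maresins MaR1 and MaR2: 2
- "protectins: PD1 and PDX; lipoxins (LX): LXA4, and LXB4; prostaglandins: PGE2, PGD2 and PGF2α; thromboxane TXB2; and leukotriene LTB4": 2 + 2 + 3 + 1 + 1 = 9
- Analytes: 9 + 7 + 7 + 2 + 9 = **34**
- Clinical measures: FSS 1 ("Fatigue will be measured with the FSS"), mMRC 1, MIP and MEP 2, 6MWT with the two 30-second tests 3, OASIS and ODSIS 2: **9**
- Total: 34 + 9 = **43**, at one between-arm test each.

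**Expected false positives if no secondary outcome is truly affected** (k × 0.05; this holds at any correlation):

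- 43 tests: 2.15
- 34 analytes: 1.70
- 9 clinical measures: 0.45

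**Chance of at least one, independent tests** (1 − 0.95^k):

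- 43 tests: 0.890
- 34 analytes: 0.825
- 9 clinical measures: 0.370

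**Effect of correlation.** The article gives no correlations, so these values are assumed. Each figure comes from 200,000 simulated sets of 43 two-sided null z-tests. In the two-block column, analytes and clinical measures are correlated within their own block only.

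| Assumed correlation | All 43 together | Two blocks |
|---|---|---|
| 0.1 | 0.87 | not run |
| 0.3 | 0.77 | 0.80 |
| 0.5 | 0.59 | 0.66 |
| 0.7 | 0.38 | 0.49 |

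**Effect of some real differences** (independent tests):

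- 33 true nulls: 0.82
- 22 true nulls: 0.68
- 10 true nulls: 0.40

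**Counting only false positives that favour the supplement** (0.025 each, independent, all nulls true): 1 − 0.975^43 = 0.66.

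**The case against.** **False positives almost certain?** A reader might infer this from 89%. The documents do not support it. The 89% is the ceiling: it needs 43 independent tests and no true effect on any outcome. Analytes from shared pathways and related clinical scales are probably correlated. The no-effect assumption is also implausible for part of the panel. 17-HDHA, 14-HDHA and 18-HEPE appear to be the mediators that the Nutritional Intervention section says the supplement contains, so a difference there would mainly show exposure. Both points stand, and both lower the figure.

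**Within-arm tests.** Adding the paired tests in each arm gives 43 × 3 = 129 tests and 0.999 under independence. That figure should not be used. The Discussion expects change in both arms, so the within-arm nulls are not credible.

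**Are 34 separate declarations planned?** The article does not say so outright. Secondary outcomes describes a profile, and Sample size calculation treats inflammation as one binary comparison of patients whose balance changed. This is a fair reservation about the exact count. Separate tests nevertheless remain the natural reading of the Statistical analysis section, and nothing there limits the analyte testing to a summary.

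**A plan to turn chance hits into claims?** A reader might see one in the Discussion. It states a mechanistic expectation and does not plan to build claims on isolated analytes.

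**The unseen analysis plan and common practice.** An adjustment may exist in a document that is not shown, and nominal reporting of secondaries with a caveat is common and acceptable when they are labelled exploratory. The caveat is present here; the label is not. The article also fixes a threshold, so it is not merely silent. If an adjustment exists elsewhere, these two sections should say so.

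**Conclusion.** The point holds as a limited one. A single unadjusted threshold is stated for 43 secondary outcomes, its effect is acknowledged, and nothing is done about it. If none of the 43 were affected, about two false positives would be expected. The chance of at least one would then be 59% to 77% at assumed common correlations of 0.5 to 0.3, with 89% as the ceiling. Real effects on some outcomes reduce both the expected number and the chance. The calculation assumes one between-arm test per listed outcome.

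The consequence is confined to claims made from secondary outcomes. The primary endpoint and its sample size are untouched.

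**What to change.** Before unblinding, replace the limitation sentence with a decision rule, and put the same rule in Statistical analysis:

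- **Analyte panel:** declare findings among the 34 analytes by Benjamini-Hochberg at a 5% false discovery rate. The ordered p-values are compared with 0.05 × i/34, so a lone finding needs p ≤ 0.05/34 = 0.0015.
- **Other secondary outcomes:** report the between-arm difference with its 95% confidence interval and label it exploratory.
- **Optional:** if the sponsor wants to make claims from clinical secondaries, pre-specify a short list tested in a fixed order or with Holm's adjustment. Which measures go on it, and in what order, is the sponsor's choice; several schemes are defensible.

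This needs no additional patients or measurements, only a change of wording. The cost is that some results with p<0.05 can no longer be claimed as findings.
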